### Background and research question

Acute coronary syndromes (ACS), comprising both ST elevation myocardial infarction (STEMI) and non-ST elevation myocardial infarction (non-STEMI) are a significant cause of morbidity, mortality and cost to the community. In fact, ACS are the leading cause of mortality in Australia (5). In 2013-14 there were 104,100 hospitalisations for ACS (5). Direct hospitalisation costs are estimated at \$1.8 billion, with total economic costs around \$17.9 billion annually (6). People in rural and remote areas are 60% more likely to be hospitalised with ACS than people in major cities, and the mortality rate is also higher (5). Rural patients hospitalised for ACS often require hospital transfers, which add further burden on the ambulance and hospital systems and local community. Timely access to evidence-based and optimal ACS management, in both the acute and chronic phases of ACS, is imperative for optimal clinical care (7).

The failure to treat ACS, in particular STEMI, is a significant issue nationally. In the Snapshot-ACS study, failure to treat STEMI occurred in 36.8% of patients (1). Failure to treat in the acute phase resulted in a doubling of mortality (2). This preventable mortality, due to clinical variation, was not able to be more accurately quantified within the study design of Snapshot-ACS, but there are clearly medical, social and economic costs associated with suboptimal treatment of ACS.

Local causes for failure to treat STEMI in HNELHD have been collected after a systematic review of ACS avoidable deaths from the Clinical Excellence Commission in NSW. Local data has been systematically collected to better identify the problems inherent in treating ACS in the rural environment (4). The data shows a high incidence of misdiagnosis of STEMI in smaller, rural hospitals with a consequent increase in mortality. The missed acute myocardial infarction (MAMI) data indicates that failure to interpret the ECG and confused clinical judgment are the most frequent causes of failure to treat STEMI, occurring in 70% and 65% of missed STEMI cases respectively (4). We therefore propose to support diagnosis and clinical decision making in smaller rural hospitals to prevent missing the diagnosis of STEMI.

**Aims:** To improve identification and management of patients with ACS in rural hospitals across 3 LHDs by implementing a hub and spoke ACS management system.

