### **Hypotheses:**

1. The MORACS program will improve identification of STEMI
2. The MORACS program will improve 30-day mortality, 12-month mortality, time to reperfusion, length of hospital stay and readmission rates in patients with suspected ACS presenting to rural hospitals

Our proposal addresses a variation in clinical care that is deadly, costly, potentially preventable. Hub-and-spoke models have been shown to be effective in other clinical situations, but our application is a novel use of this approach. Our telehealth solution to this clinical issue will maximise the clinical support to many rural hospitals.

The NSW State Cardiac Reperfusion Strategy (SCRS) aims to deliver increased access to medical advice and reperfusion therapies in a timely manner for patients diagnosed with STEMI. Our approach is complementary to the SCRS and will in no way overlap with this. We aim to assist clinicians earlier in the diagnostic work-up, to prevent the diagnosis being missed. If a diagnosis of STEMI is made, the patient will be treated via the usual SCRS process.

Research design and methods (maximum 4 pages)

**Study design:** A prospective, cluster randomised controlled trial (RCT) to evaluate the effectiveness of a hub and spoke ACS management system to improve health outcomes for rural residents.

**Setting:** Hunter New England Local Health District in regional/rural NSW Australia. The following hospitals will be included:

Armidale, Barraba, Bingara, Cessnock, Denman, Dungog, Glenn Innes, Gloucester, Gunnedah, Guyra, Kurri Kurri, Merriwa, Moree, Murrurundi, Muswellbrook, Narrabri, Nelson Bay, Singleton, Scone, Tenterfield, Vegetable Creek, Walcha and Wialda;

These hospitals were selected because General Practitioners (GPs) or Career Medical Officers (CMOs) manage cardiology admissions, i.e. there are no Emergency Medicine specialists at these hospitals. Together they assess over 6000 chest pain presentations per year. The rationale for including GP and CMO staffed hospitals was that these were the hospitals with higher numbers of missed myocardial infarctions in our prior study (4).

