#### **Outcomes:**

Primary Outcome: Proportion of correctly identified STEMI. ECGs will be adjudicated by a senior clinician at John Hunter Hospital in consultation with the treating clinician who has assessed the patient. All ECGs performed on all patients presenting with possible ACS will be analysed. In HNELHD, this will be performed via CAP online.

Secondary outcomes: In-hospital, 30-day and 12-month mortality, time to reperfusion (for STEMI), length of hospital stay, MACE (major adverse cardiac events: death, repeat MI or all-cause readmission) at 30-days and 12-months. Post discharge health care utilisation and medication adherence will likely be improved by better hospital care, so we will assess this by MBS and PBS linkage. Myocardial infarction will be defined by elevated troponin in the context of typical ischaemic symptoms. Mortality will be ascertained from the National Death Index (NDI). Readmissions will be captured by CHeReL. Reperfusion and revascularisation data will be ascertained from the Cardiac and Stroke Outcomes Unit in HNE.

**Measures:** Primary and secondary outcome data will be obtained from medical records and from CHeReL. We have discussed the project and received a formal quote from CHeReL. We will also link with MBS and PBS to assess post-discharge healthcare utilisation and medication prescription/adherence after hospitalisation. This will contribute valuable qualitative information as well as informing cost effectiveness analysis.

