#### **Statistical methods and analysis:**

- 1) Power calculation: Based on local data, anticipated number of presentations to hospital with suspected ACS over a 12-month period are approximately 6,300. Of these an estimated 50% will require admission and investigation for ACS. Around 15% of the total patient group will have non-STEMI and a further 5% have STEMI, i.e. ~315 STEMI per year across all centres. An estimated 36% of the patients with STEMI will be missed and we wish to detect an absolute reduction in missed STEMI of 16%, i.e. 36% down to 20%, which will require 280 participants (140 per arm), at 80% power and  $p=0.05$ . We also include a design effect of 1.24 (assuming cluster sizes of 13 and  $ICC=0.015$ ) for a total of 338 patients across 26 clusters total. Therefore, it will take approximately 15 months to recruit. In the two-year timeframe, we will be able to analyse the rate of STEMI detection (primary endpoint) and will have a *median* 12-month follow-up for the secondary endpoints.
- 2) Evaluation of Results: Analysis of the primary outcome (the proportion of correctly identified STEMI) will be via logistic regression with adjustment for stratifying variables (size and staffing of hospital), and analysis of the secondary outcomes will be via linear and logistic regression.
- 3) Economic evaluation: Assuming an improvement in STEMI identification, three economic evaluations will be conducted. 1) From a health provider perspective, a cost-effectiveness analysis to report the resources required per unit improvement in the identification of STEMI. Costs will include the cost of the intervention as well as related costs such as hospital stay,

treatments and readmissions. The measure of effect will be based on the primary outcome (identification of STEMI). 2) A cost-consequence analysis will report the cost of the intervention and its range of consequences such as the change in STEMI identification, reperfusion times, hospital admissions, readmissions and MIs. 3) A modelling exercise to estimate costs and potential downstream impacts from the intervention over a ten-year time frame, these will include avoided healthcare costs as a consequence of improved STEMI detection and treatment, as well as adherence to secondary prevention therapies. This will be informed by data linkage with MBS and PBS.

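### Time to reperfusion by linear regression compares only the STEMI patients who were reperfused, a post-randomisation subset that the programme is meant to change

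*Protocol*

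**What the plan says.** Protocol, Outcomes: the primary outcome is "Primary Outcome: Proportion of correctly identified STEMI". The secondary outcomes include "time to reperfusion (for STEMI"). No value or rule is given for a STEMI patient who is never reperfused.

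Protocol, Hypotheses: the second hypothesis begins "The MORACS program will improve 30-day mortality, 12-month mortality, time to reperfusion", so a direction is predicted for this outcome.

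Protocol, Statistical methods and analysis, item 2: "analysis of the secondary outcomes will be via linear and logistic regression". No time-to-event or competing-risk method is named.

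The protocol also links diagnosis to treatment. Under Hypotheses: "If a diagnosis of STEMI is made, the patient will be treated via the usual SCRS process". Under Background and research question: "failure to interpret the ECG and confused clinical judgment are the most frequent causes of failure to treat STEMI". The power calculation assumes "An estimated 36% of the patients with STEMI will be missed", to be reduced to 20%.

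**The concern.** Linear regression needs a number for every patient analysed, and a STEMI patient who is never reperfused has none. Applied as written, the method compares mean times among reperfused patients only. Being reperfused happens after randomisation and is largely downstream of being identified, which is what the intervention targets. If the trial succeeds, the intervention arm's reperfused group will contain patients whose counterparts in the control arm are absent from the comparison. Adjusting for the stratifying variables (hospital size and staffing) does not restore comparability.

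At stake is a named hypothesis. The mean comparison gives no credit for a patient who moves from untreated to treated, and it could show a difference in either direction that reflects who entered the comparison rather than how quickly anyone was treated.

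**Working it through.** The protocol states no figure for time to reperfusion, so there is none to reproduce. The point does not depend on how the sample size was derived; the total of 338 is used only for scale.

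**Inputs from the protocol** (Statistical methods and analysis, item 1): missed STEMI 36% versus 20%, so identified 64% versus 80%; 338 STEMI in total, or 338/2 = 169 per arm if equal.

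**Size of the subsets**, if every identified and no missed STEMI were reperfused (an approximation):
- Control: 169 × 0.64 ≈ 108 with a time, 61 without.
- Intervention: 169 × 0.80 ≈ 135 with a time, 34 without.
- Additional intervention patients: 135 − 108 = 27, which is 20% of that arm's analysed group.

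**Illustration A: no missed patient is reperfused.** Assume a mean of 60 min for patients identified in either arm, nobody slowed, and additional patients at a mean of L min. The control mean is 60. The intervention mean is (0.64 × 60 + 0.16 × L)/0.80.

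| L (assumed) | Intervention mean | Apparent difference | Difference if those identified anyway are also 10 min faster |
|---|---|---|---|
| 90 | 66 | +6 | −2 |
| 120 | 72 | +12 | +4 |
| 180 | 84 | +24 | +16 |

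The last column is (0.64 × 50 + 0.16 × L)/0.80 − 60. A speed-up of 0.16/0.64 = one quarter of the extra delay (L − 60) cancels the apparent slowing.

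**Illustration B: half of the missed patients in each arm are reperfused late, at an assumed 240 min**, with additional patients at 150 min. Per 100 STEMI per arm:
- Control: (64 × 60 + 18 × 240)/82 = 99.5 min.
- Intervention: (64 × 60 + 16 × 150 + 10 × 240)/90 = 96 min.
- Difference: −3.5 min. Without the late reperfusions, the same 150 min gives (64 × 60 + 16 × 150)/80 = 78, a difference of +18 min. The sign reverses on an assumption about which the protocol says nothing.

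**Direction of the bias.** Suppose the programme acts only by moving 16 patients from missed to identified. In B, 18 − 10 = 8 of them would have been reperfused late anyway, and 16 − 8 = 8 are newly reperfused. Among the 82 who would be reperfused under either allocation, the true mean change is 8 × (150 − 240)/82 = −8.8 min. The comparison shows −3.5, so it is biased against the programme. If the 16 are instead treated at 60 min, the true change is 8 × (60 − 240)/82 = −17.6 min. The intervention mean is (80 × 60 + 10 × 240)/90 = 80 min and the observed difference is 80 − 99.5 = −19.5, so the bias favours the programme.

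**With all STEMI in the denominator.** The proportions ever reperfused are 64% versus 80% in A, and 82% versus 90% in B. In B the cumulative proportions are 64% in both arms at 60 min, 64% versus 80% at 150 min, and 82% versus 90% at 240 min. If nobody is treated later than under usual care, the intervention curve is never below control, so an apparent slowing cannot arise from selection.

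**The case against.** The strongest objection is that the statistical sentence is one generic clause for all secondary outcomes. It does not tie a model to this endpoint, and handling of untreated patients and competing events is commonly left to an SAP, which was not available here. That stands in part: exclusion of never-reperfused patients is inferred, not stated. But the protocol does name the methods. No time threshold is given that would turn this outcome into a yes/no variable for logistic regression, so linear regression is the natural reading. An SAP that followed the sentence would keep the problem.

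Three stronger readings are tempting, and the documents do not support them:

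- **That 36% of control and 20% of intervention STEMI would drop out.** These are rates of missed STEMI, not of never being reperfused. No time limit is set on correct identification, so a patient missed at first may be reperfused late, and an identified patient may not be reperfused. The background figure ("failure to treat STEMI occurred in 36.8% of patients") is close to 36%, but the protocol does not equate the two.
- **That the programme will appear to slow treatment because the additional patients are harder or later cases.** Nothing in the protocol says so. Under Allocation to treatment, the reading clinician is notified automatically at triage, so these patients need not be recognised later. Missed cases are attributed to ECG interpretation and clinical judgment, not late presentation.
- **That the times needed are already collected.** The Outcomes section mentions reperfusion and revascularisation data; no clock start is specified.

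It is also fair that the benefit of more patients being identified is captured by the primary outcome, and that mortality and MACE are separate secondary outcomes. The defect is confined to this one secondary outcome and leaves the primary analysis and the sample size untouched.

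**Conclusion.** The point holds as a poorly chosen method for one hypothesised secondary outcome. The stated analysis leads to a comparison of means among reperfused patients, whose selection depends largely on identification, planned at 64% versus 80%. That comparison is not protected by randomisation, and an unknown direction of bias does not make it safe.

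Neither size nor direction can be fixed from the protocol. All minutes above are assumptions; only the identification rates and the total of 338 come from the document. Within those assumptions, the apparent effect ranges from a 24 min slowing to a 19.5 min gain, and the part due to selection can run either way. The change should be made, but it does not threaten the trial's main conclusion.

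**What to change.** In Statistical methods and analysis, item 2, give time to reperfusion its own sentence:

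- Include all adjudicated STEMI in both arms.
- Analyse reperfusion as time-to-event from ED presentation, using cumulative incidence with death as a competing event and never-reperfused patients kept as not reperfused, allowing for clustering by hospital.
- Report the proportion of all STEMI reperfused, by arm.
- Report time among reperfused patients as descriptive only.

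The cost is slightly more analysis work. The sponsor must also confirm that ED presentation and reperfusion times will be extracted from the registration system, the medical records and the reperfusion data source already named in the protocol. Deaths are already to be ascertained from the National Death Index. The sample size does not change.

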#### **Statistical methods and analysis:**

- 1) Power calculation: Based on local data, anticipated number of presentations to hospital with suspected ACS over a 12-month period are approximately 6,300. Of these an estimated 50% will require admission and investigation for ACS. Around 15% of the total patient group will have non-STEMI and a further 5% have STEMI, i.e. ~315 STEMI per year across all centres. An estimated 36% of the patients with STEMI will be missed and we wish to detect an absolute reduction in missed STEMI of 16%, i.e. 36% down to 20%, which will require 280 participants (140 per arm), at 80% power and  $p=0.05$ . We also include a design effect of 1.24 (assuming cluster sizes of 13 and  $ICC=0.015$ ) for a total of 338 patients across 26 clusters total. Therefore, it will take approximately 15 months to recruit. In the two-year timeframe, we will be able to analyse the rate of STEMI detection (primary endpoint) and will have a *median* 12-month follow-up for the secondary endpoints.
- 2) Evaluation of Results: Analysis of the primary outcome (the proportion of correctly identified STEMI) will be via logistic regression with adjustment for stratifying variables (size and staffing of hospital), and analysis of the secondary outcomes will be via linear and logistic regression.
- 3) Economic evaluation: Assuming an improvement in STEMI identification, three economic evaluations will be conducted. 1) From a health provider perspective, a cost-effectiveness analysis to report the resources required per unit improvement in the identification of STEMI. Costs will include the cost of the intervention as well as related costs such as hospital stay,

treatments and readmissions. The measure of effect will be based on the primary outcome (identification of STEMI). 2) A cost-consequence analysis will report the cost of the intervention and its range of consequences such as the change in STEMI identification, reperfusion times, hospital admissions, readmissions and MIs. 3) A modelling exercise to estimate costs and potential downstream impacts from the intervention over a ten-year time frame, these will include avoided healthcare costs as a consequence of improved STEMI detection and treatment, as well as adherence to secondary prevention therapies. This will be informed by data linkage with MBS and PBS.

**Considerations about Aboriginal and Torres Strait Islander Peoples:** Aboriginal and Torres Strait Islander Peoples have disproportionately higher rates of ACS, and these occur at a younger age than in non-Indigenous people (8). In rural settings, Aboriginal and Torres Strait Islander Peoples make up a higher percentage of the population. Our project has been thoroughly discussed with and reviewed by the Aboriginal Health Unit of the HNE LHD. Improving diagnosis, management and outcomes for rural ACS patients will disproportionately advantage Aboriginal and Torres Strait Islander Peoples.

**Implications for Ambulance:** NSW ambulance service (NSWAS) have been consulted and are a partner for this project. Existing ambulance work flows will not be changed. With increased diagnosis of STEMI, there will be a higher rate requirement for urgent transport to a Primary PCI centre, under the SCRS. It is estimated this will be an additional 60 STEMI patients over the 15 months recruitment period. Ambulance will benefit from earlier notice of transfer in non-STEMI patients, which will improve workflow. Ambulance have requested data on outcomes to inform their practice, and we will provide data on ambulance transported patients back to NSWAS.

**Governance structure:** The project will be supervised by the MORAC steering committee. The steering committee will comprise project investigators, partner representatives, clinicians, operational managers, clinical stream and clinical governance representatives and will meet bi-monthly.

There will be two distinct working groups operating under the steering committee: the research working group and the system implementation group. Both groups will report to the MORAC steering committee.

The research working group will be chaired by the Chief Investigator and will have membership of senior academic staff who will monitor the ongoing design and implementation of the project. This group will meet on a monthly basis.

The System Implementation Group will be chaired by the Head of Cardiology at John Hunter hospital. It will be comprised of clinicians, including the chief investigator, and operational staff to ensure stakeholder communication and address system problems. This group will meet on a fortnightly basis to oversee individual clinical cases and system development. Importantly, this group will also provide feedback to the clinicians reading the ECG and troponin results, at both an individual case level and at the aggregated data level, to maintain optimal adherence to the process.

A clinical events committee (CEC) of experienced cardiologists will also adjudicate all clinical events in a blinded fashion at Monash University. As blinding will not be possible with the system implementation group who review outcomes, scientific rigour demands a blinded review to confirm events. Monash will also provide an ECG core lab reading service. This will provide the most rigorous oversight of the trial. Disagreements on ECG reading will be resolved by consensus at Implementation Group meeting.

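### The sample-size figures do not come from one calculation: the design effect and recruitment time do not follow from their inputs, and 23 listed hospitals in one district stand against 26 clusters and three districts

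*Protocol*

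**What the plan says.** The power calculation (Statistical methods and analysis, item 1) expects about 6,300 presentations a year, of which 5% are STEMI, so about 315 a year over all centres. It states "An estimated 36% of the patients with STEMI will be missed" and aims to detect an "absolute reduction in missed STEMI of 16%, i.e. 36% down to 20" per cent. It puts the unclustered requirement at 280 (140 per arm) for 80% power at p = 0.05. It goes on: "We also include a design effect of 1.24 (assuming cluster sizes of 13 and" an ICC of 0.015), "for a total of 338 patients across 26 clusters total". The next sentence is "Therefore, it will take approximately 15 months to recruit".

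The Setting paragraph places the trial in Hunter New England LHD and names the hospitals, beginning "Armidale, Barraba, Bingara, Cessnock, Denman, Dungog, Glenn Innes, Gloucester, Gunnedah, Guyra"; the full list has 23 names. The same paragraph credits these hospitals with more than 6,000 chest pain presentations a year. The Participants paragraph also confines the trial to that district. The Aims, however, speak of work "across 3 LHDs by implementing a hub and spoke ACS management system", and the section on expected impacts again refers to three rural LHDs. The protocol neither names the other two districts nor lists hospitals in them.

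Under Implications for Ambulance, the extra urgent transport load is given as follows: "It is estimated this will be an additional 60 STEMI patients over the 15 months recruitment period".

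**The concern.** Design effect, total, number of clusters and duration should form one chain, each following from the one before. Here the design effect does not follow from the cluster size and ICC beside it, the duration does not follow from the total and the yearly rate, and the cluster count disagrees with the hospital list.

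At stake is what the protocol fixes: how many hospitals are randomised and in which districts, how many STEMI cases the primary analysis should expect, and whether data collection ends after a period or at a count. A statistician or ethics committee could not tell from the text which figures are in force. The ambulance partner also relies on a number tied to the same period.

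**Working it through.** **Inputs (power calculation unless noted).** Missed STEMI 36% v 20%; 280 unclustered; cluster size m = 13; ICC 0.015; design effect 1.24; N = 338; 26 clusters; about 315 STEMI a year; about 15 months. From the Setting: 23 hospitals, one district. Sidedness of the test is not stated; two-sided is assumed here.

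**1. Unclustered size.** n per arm = [1.96·√(2·p̄·q̄) + 0.84·√(p₁q₁ + p₂q₂)]² / d², with p̄ = 0.28 and d = 0.16. This gives 123 per arm (246 in all), or 135 per arm (270) with continuity correction. The stated 140 per arm is somewhat larger; without the correction it has 85% power. It is taken as given below and errs on the safe side.

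**2. Design effect.** DE = 1 + (m − 1) × ICC = 1 + 12 × 0.015 = **1.18**, against 1.24 stated. To obtain 1.24:
- at m = 13, ICC = 0.24 / 12 = 0.020;
- at ICC 0.015, m = 1 + 0.24 / 0.015 = 17.

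**3. Total and clusters.**
- With 1.18: 280 × 1.18 = 330.4; 330.4 / 13 = 25.4, rounded up to 26 clusters; 26 × 13 = **338**, as stated.
- With 1.24: 280 × 1.24 = 347.2; 347.2 / 13 = 26.7, or 27 clusters.

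So 280, 13, 0.015, 26 and 338 agree with each other, and 1.24 is the outlier in that chain.

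**4. Recruitment time.** 338 / 315 × 12 = **12.9 months**. Fifteen months gives 315 × 15 / 12 = 393.75, about **394** STEMI, which is 56 more than 338 (17%).

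**5. Hospitals and districts.** 23 names against 26 clusters; one district in the Setting and Participants paragraphs against three in the Aims and the impact section. Over 23 hospitals, 338 patients are 14.7 per hospital (DE 1.205), and 394 are 17.1 per hospital (DE = 1 + 16.1 × 0.015 = 1.24).

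**6. Power for 36% v 20%, ICC 0.015, equal cluster sizes.** Effective n per arm = (N / 2) / DE; normal reference, or noncentral t with clusters − 2 df.

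| N | Clusters | DE | Normal | t |
|---|---|---|---|---|
| 338 | 26 | 1.18 | 86% | 84% (24 df) |
| 338 | 23 | 1.205 | 85% | 82% (21 df) |
| 394 | 23 | 1.24 | 89% | 87% (21 df) |

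**7. Unequal cluster sizes (sensitivity only).** DE = 1 + [(1 + CV²)·m − 1] × ICC. The CV of STEMI counts is not in the protocol, so a range is assumed. For 338 in 23 clusters:

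| Assumed CV | DE | Normal | t, 21 df |
|---|---|---|---|
| 0.4 | 1.24 | 84% | 81% |
| 0.6 | 1.28 | 83% | 80% |
| 0.8 | 1.35 | 81% | 78% |

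**8. Ambulance figure.** 0.16 × 394 = 63, close to the stated 60. That product applies the effect to every STEMI patient. If about half the patients are in intervention hospitals, the same effect gives 0.16 × 394 / 2 = about 32.

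**The case against.** The strongest reply is that most of the chain holds. As step 3 shows, the stated 338 and 26 clusters follow from 280, a cluster size of 13 and the ICC once rounded up to whole clusters; only 1.24 is misprinted. Fifteen months exceeds the 12.9 needed, so it errs on the safe side and might include start-up time. The protocol sets no rule to stop at 338 and enrols all consecutive patients. All of this stands, with two limits. The 15 months is presented as a consequence of the preceding figures and no allowance is stated. And the hospital and district conflicts remain whichever design effect is meant.

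A reader might infer that 23 hospitals of 13 supply only 299 patients and miss the target. The documents do not support this. The 23 listed hospitals are themselves credited with over 6,000 presentations a year, in line with the 6,300 behind the 315 STEMI, so fewer hospitals mean larger clusters, not fewer patients.

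A reader might also infer that the trial is underpowered. At N = 338 that needs both a t reference, which the protocol does not specify, and an assumed CV of about 0.6 or more. The range of 0 to 100 beds makes equal cluster sizes unlikely, but beds are not STEMI counts and fix no CV.

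On the ambulance figure, the protocol gives no derivation for 60. That it is 16% of all STEMI patients is inference: a reason to ask for the basis, not proof of an error.

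**Conclusion.** The point holds as an inconsistency in figures the trial relies on. Three parts are firm and need no outside assumption: the design effect is 1.18 on the stated inputs, not 1.24; 338 patients at the stated rate take 12.9 months, not 15; and 23 hospitals in one district conflict with 26 clusters and three districts. The gap in total N is small, since 338 is within 3% of both 330 and 347.

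No underpowering is claimed. At the stated ICC and equal cluster sizes, power at N = 338 exceeds 80% with either 23 or 26 clusters and with either reference distribution.

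The document cannot show which figure is the slip. That 23 hospitals over 15 months return a design effect of 1.24 suggests that two calculations were mixed, but does not prove it. The estimate of 60 additional STEMI is doubtful, with about 32 as the alternative if roughly half the patients are in intervention hospitals; the sponsor needs to check it.

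**What to change.** Restate ICC, mean cluster size, design effect, N, number of clusters and recruitment time from one calculation, and make the hospital list and number of LHDs agree throughout. Two consistent options are:

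- **(i)** 26 hospitals, with the missing three listed and their district named; m = 13, DE 1.18, N = 338, about 13 months.
- **(ii)** The 23 listed hospitals for 15 months; about 394 STEMI, m about 17.1, DE 1.24, power about 89% (normal reference) or 87% (t on 21 df) at equal sizes, with the references to three LHDs corrected.

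The choice is the sponsor's. In either case, state whether recruitment ends at the fixed duration or at the target N; if 15 months is kept with 338, state the allowance that explains the difference. A sensitivity figure for unequal cluster sizes, with its assumed CV, may be added.

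Give the basis for the ambulance estimate, check whether it counts intervention hospitals only, and restate it if needed.

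The cost is protocol wording and a note to the ambulance partner. Option (ii) stays within the 15 months already planned; option (i) shortens recruitment by about two months but requires three more hospitals to be identified.

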**Follow-up:** All patients will have outcomes data recorded at hospital discharge or hospital transfer in the medical record. Thirty-day and 12-month readmission rates (and reasons) will be identified through the Centre for Health Record Linkage (CHeReL). Deaths will be identified through the National Death Index. No individual patient follow-up will be performed.

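### Logistic regression of mortality and MACE at a fixed 12 months does not fit a two-year timeframe that gives only a median of 12 months' follow-up

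*Protocol*

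**What the plan says.** Three statements in the protocol bear on this point.

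- **Endpoints.** Under Outcomes, the secondary outcomes include "In-hospital, 30-day and 12-month mortality", and MACE is set at the same two post-discharge time points, 30 days and 12 months. The Follow-up paragraph adds that "Thirty-day and 12-month readmission rates (and reasons) will be identified through the Centre for Health Record Linkage", with deaths taken from the National Death Index and no individual patient follow-up. Hypothesis 2 names 12-month mortality.
- **Method.** Under Statistical methods and analysis, item 2, "analysis of the secondary outcomes will be via linear and logistic regression". No time-to-event method is named. The protocol does not match each outcome to a model, but logistic regression is the natural reading for mortality and MACE.
- **Follow-up.** Item 1 says "it will take approximately 15 months to recruit", and the paragraph on implications for the ambulance service repeats the 15-month period. Item 1 then says that within a two-year timeframe the trial "will have a *median* 12-month follow-up for the secondary endpoints". The emphasis on the word median is the protocol's own.

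**The concern.** A logistic model of status at 12 months needs each patient's status at 12 months. With a median follow-up of 12 months, about half of the patients are observed for less. The stated method and the stated follow-up therefore do not fit, and each simple way of running the model on incomplete follow-up has a cost:

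- coding short follow-up as event-free understates the 12-month risk;
- excluding only patients whose status is unknown, while keeping those with an early event, overstates it;
- excluding every patient recruited too late to reach 12 months leaves the risk unbiased if risk does not drift with calendar time, but gives up data.

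The 12-month risks of death and MACE are part of Hypothesis 2, and readmissions and infarctions also enter the cost-consequence analysis.

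**Working it through.** **Inputs.** Recruitment of about 15 months, a two-year timeframe and a median follow-up of 12 months come from item 1 of Statistical methods and analysis. Uniform accrual, the lag L, the constant hazard and the 12-month risks of 10% and 30% are assumptions; the protocol gives none of them. L is any start-up or linkage delay, in months, inside the 24.

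**1. The plan's own median.** Follow-up runs from 24 − 15 − L = 9 − L to 24 − L months, so the median is 16.5 − L.

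- With L = 0 the range is 9 to 24 months and the median is 16.5, not 12.
- A median of 12 requires L = 16.5 − 12 = 4.5, which gives a range of 4.5 to 19.5 months.

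**2. Share followed for under 12 months.** This is (12 − (9 − L))/15 = (3 + L)/15.

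- L = 0: 3/15 = 20%
- L = 1.5: 30%
- L = 3: 40%
- L = 4.5: 7.5/15 = 50%

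**3. Share of 12-month events not yet observed.** For low risk under a constant hazard this is 1 minus the mean of min(f, 12)/12, where f is follow-up.

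- L = 0: the 20% who fall short average 10.5 months. 0.80 + 0.20 × 10.5/12 = 0.975, so 2.5% are unobserved.
- L = 4.5: the 50% who fall short average 8.25 months. 0.50 + 0.50 × 8.25/12 = 0.844, so about 16% are unobserved.

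**4. Effect on the estimated risk.** With hazard λ = −ln(1 − risk)/12:

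- observed event proportion = mean of 1 − exp(−λ·min(f, 12));
- unknown-status share = mean of exp(−λf) over patients with f < 12, counted as zero for the others.

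Coding short follow-up as event-free reports the observed proportion. Dropping only unknown-status patients reports observed/(1 − unknown).

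| Lag | True 12-month risk | Status unknown | Coded event-free | Unknown dropped, early events kept |
|---|---|---|---|---|
| 0 | 10% | 18.2% | 9.8% | 9.76/81.8 = 11.9% |
| 0 | 30% | 14.6% | 29.4% | 29.36/85.4 = 34.4% |
| 4.5 | 10% | 46.5% | 8.5% | 8.49/53.5 = 15.9% |
| 4.5 | 30% | 39.2% | 25.8% | 25.79/60.8 = 42.4% |

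**5. Precision if all late recruits are dropped.** Ignoring clustering, standard errors grow by 1/√0.8 = 1.12 (12%) with no lag and by 1/√0.5 = 1.41 (41%) at the stated median. With clustering the loss is smaller.

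**6. When 12 months is complete for everyone.** Last enrolment plus 12 months is 15 + 12 = 27 months from first enrolment. Counted on the two-year clock it is 27 + L: month 27 with no lag (3 months beyond 24) and month 31.5 with L = 4.5 (7.5 months beyond).

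**The case against.** The strongest reply is that no data cut is fixed. Item 1 describes what will be available in two years. It does not say that the 12-month analysis closes then, nor that incomplete patients enter the model. Outcomes come from record linkage, so they can be extracted once everyone has reached 12 months, and the extraction date could be set in a statistical analysis plan that is not at hand. This stands in part, because waiting is an open route and the better one. It does not remove the mismatch: the protocol ties secondary follow-up to the two-year timeframe, describes it by a median, and names only methods that assume complete status.

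Three further points stand and limit the size.

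- A reader might infer that half of the patients will have no 12-month status. The documents do not support that as the expected figure. It needs the literal median of 12 and an unstated lag of about 4.5 months; the stated timeline with no lag gives 20%. Patients with an early event have known status, so the unknown share is lower still. Nor is the median of 12 a proven error, since a start-up or linkage delay inside the two years would explain it.
- A reader might infer that the comparison between arms is biased. The design is a parallel cluster trial of consecutive patients, and no staggered hospital start is described. A shortfall set by calendar date should be similar in both arms.
- The constant hazard is an assumption. If events cluster early, fewer are lost than shown.

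**Conclusion.** The concern holds in a limited form. The protocol's fixed 12-month endpoints, its choice of logistic regression and its median follow-up do not fit together as written. Under uniform accrual, between about 20% (no lag) and about 50% (the stated median of 12) of patients would have under 12 months' follow-up at two years, with about 2.5% to 16% of 12-month events unobserved under a constant hazard. The share whose status is truly unknown is somewhat lower: about 15% to 18% and 39% to 47% respectively, at assumed risks of 30% and 10%.

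The harm is to absolute risks and to precision. Its direction depends on how incomplete patients are handled. A distorted treatment comparison is not shown. The primary outcome and the 30-day outcomes are unaffected. The point deserves correction before analysis, but it does not threaten the trial's main result.

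**What to change.** Replace the statement about median follow-up with a linkage extraction date that covers at least 12 months after the last patient's presentation, for all linked sources. State that the 12-month logistic analyses run only on that extract. If recruitment takes 15 months, the extract must reach month 27 from first enrolment; on the two-year clock, add any lag. Tying the rule to the last presentation rather than to a calendar month keeps it right if recruitment runs over.

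The cost is a delay of about 3 to 7.5 months for the 12-month results only. No patient contact is needed, and the primary and 30-day results need not wait.

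If the two-year report must include 12-month outcomes, analyse mortality and MACE by a time-to-event method with censoring at the data cut and allowance for clustering (for example a shared-frailty or cluster-robust Cox model), with Kaplan-Meier 12-month risks by arm. This avoids the delay, but it changes the effect measure from an odds ratio to a hazard ratio and requires event dates, including dates of repeat infarction.
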